#### Neurocognitive functioning

The neurocognitive tests are a combination of neuropsychological tests for which normative data were published, so that patient’s performance can be corrected according to age, gender and education. We will compare the raw data between the treatment arms with a t-test. Test scores can be transformed into z-values using normative data and compared with a one sample t-test. With no-normal distributions the appropriate statistical tests will be used.

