### Study outline

A timeline of the study is shown in figure 3. Eligible patients are approached in an outpatient setting by specialised nurses in consultation with the treating neurosurgeon. The study is explained and written information is provided (online supplemental files S2,3). After written informed consent by the coordinating investigator or principle investigators, patient characteristics (age, gender, educational level, medical background, medication use, tumour type and tumour location) are recorded. The informed consent form includes consent for collection for blood sample and residual tumour tissue. Before start of intervention, a baseline study visit is planned that includes a structured psychiatric interview, different self-report questionnaires, and neurocognitive tests. A selection of the questionnaires can be filled out online via the web-based database programme Castor Electronic Data Capture (EDC; Castor, Amsterdam, The Netherlands). The intervention starts on the day of hospital admission, concurrent with the dexamethasone treatment 1 day prior to planned surgery. 5 days postoperatively – or earlier at discharge – a structured psychiatric interview and neurocognitive screening are conducted, and questionnaires are filled out. The study medication is provided to the patients according to clinical care and is continued as long as dexamethasone is prescribed. A follow-up visit is planned 5 to 8 weeks postoperatively coinciding with the regular care assessment, at which a structured psychiatric interview and neurocognitive tests are performed and different questionnaires are filled out. Study visits take place at the medical centre of treatment. 2 weeks and 3 months postoperatively questionnaires can be filled out online via Castor EDC. Study duration from start of intervention until completion of the last questionnaires is 3 months. The study schedule is shown in table 1. In case the baseline study visit is planned the day before surgery, no neurocognitive tests will be performed – instead a neurocognitive screening may be performed – and presentation of the questionnaires is depend on the patients’ psychological and physical condition. To improve adherence the follow-up visits are coinciding with the regular care assessments.

10.1136/bmjopen-2021-054405.supp2Supplementary data

10.1136/bmjopen-2021-054405.supp3Supplementary data

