#### Neurocognitive assessment

To assess the cognitive domains verbal memory, executive functioning and attention, we used the following standardised neurocognitive tests: Hopkins Verbal Learning Test–Revised—Free Recall,^38^ Trail Making Test A and B,^39^ Controlled Oral Word Association^40^ and Medical Outcome Study (MOS) cognitive functioning scale.^41^ Raw scores can be transformed into z-scores in order to compare patients’ performance to control participants (and can be corrected for demographic variables, such as age and education).

The Montreal Cognitive Assessment (MoCA) is a cognitive screening instrument for mild cognitive dysfunction.^42^ It measures different cognitive domains; attention and concentration, executive functions, memory, language, visuoconstructional skills, conceptual thinking, calculations and orientation. The total score is 30 points; a score of ≥26 is a normal score.

The Aphasia Bedside Check (ABC) is a 10 minute screening tool that globally determines the presence of aphasia with 7 items for language comprehension and 7 items for language production.^43^ This screening will only be performed in patients who have a left-sided brain tumour with (hetero-) anamnestic language problems. With ≥3 mistakes, an aphasia may be present and the patient should not be included in the study.

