### Secondary outcomes

Secondary outcomes are neuropsychiatric symptoms, quality of sleep, HRQoL, and neurocognitive functioning 5 days postoperatively – or earlier at discharge –, 2 weeks, 5 to 8 weeks, and 3 months postoperatively. Furthermore, neuropsychiatric history, SAEs, prescribed (psychiatric) medication and referrals or evaluations of psychiatrist/psychologist will be collected. In addition, the laboratory measurements are considered secondary outcomes.

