#### Mini-screen, HADS, PANAS, ASRM, NPI-Q, DOS, LSEQ and HRQoL

Both treatment arms will be compared over time using analysis of repeated measures, GEE when outcome is dichotomous and mixed linear models for continuous outcomes.

Explanatory univariable and multivariable regression analysis will be used to identify (baseline) predictors of treatment response. Sensitivity analysis will be performed using multiple imputation to handle missing data. Any difference with a p<0.05 will be considered significant. A better outcome on the different scales in the hydrocortisone group would be considered a positive result.

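### The between-arm comparison of the neurocognitive tests leaves out the baseline scores that the trial collects, and so gives up precision

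*Protocol article*

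**What the plan says.** All references are to the protocol article.

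- **Neurocognitive functioning** (planned analyses) gives the arm comparison: "We will compare the raw data between the treatment arms with a t-test". It adds an optional step: "Test scores can be transformed into z-values using normative data and compared with a one sample t-test". Its only other provision is that other tests will be used if distributions are not normal.
- **Neurocognitive assessment** gives the purpose of the standardised scores: "Raw scores can be transformed into z-scores in order to compare patients’ performance to control participants".
- **Study outline** and **Table 1** place the tests at two times. Before the intervention, "a baseline study visit is planned that includes a structured psychiatric interview, different self-report questionnaires, and neurocognitive tests". The second time is the visit 5 to 8 weeks after surgery, "at which a structured psychiatric interview and neurocognitive tests are performed and different questionnaires are filled out".
- **Study outline** also makes an exception: "In case the baseline study visit is planned the day before surgery, no neurocognitive tests will be performed".
- For the other listed scales, the section on the mini-screen, HADS, PANAS, ASRM, NPI-Q, DOS, LSEQ and HRQoL says: "Both treatment arms will be compared over time using analysis of repeated measures, GEE when outcome is dichotomous and mixed linear models for continuous outcomes". The BPRS section likewise gives the continuous BPRS a mixed linear model. The neurocognitive tests appear in neither.
- **Secondary outcomes** gives the status of the endpoint: "Secondary outcomes are neuropsychiatric symptoms, quality of sleep, HRQoL, and neurocognitive functioning".

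**The concern.** A two-sample t-test on follow-up scores treats all stable differences between patients as noise. Where the same patient took the same test before treatment, part of that noise can be removed at no cost in data. The article does this for its other repeated scales and gives no reason for treating the neurocognitive tests differently.

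At stake is the precision of a secondary treatment comparison. A real difference is more likely to be missed, and a baseline imbalance that arises by chance passes into the estimate.

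The one-sample test adds a smaller risk. It contains no contrast between arms, so without a label its results could be read as if they compared the arms.

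**Working it through.** **1. Figures in the article.** It states none for the neurocognitive analysis. Its sample size for the primary outcome gives a number of patients to work with. With 40% against 20%, two-sided α = 0.05, 80% power, pooled variance and no continuity correction:

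n = [1.960·√(2·0.3·0.7) + 0.842·√(0.4·0.6 + 0.2·0.8)]² / 0.20² ≈ 81.2, so 82 per arm, as stated.

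I use 82 per arm below. The number tested at 5 to 8 weeks may differ.

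**2. Precision of the stated t-test.** In units of the between-patient SD, the standard error of the arm difference is √(2/82) = 0.156. The difference detectable with 80% power is (1.960 + 0.842)·0.156 = 0.44 SD.

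**3. Effect of using baseline.** Let r be the correlation between baseline and 5 to 8 week scores. The article does not give r, so a range is assumed. Adjustment multiplies the variance by 1 − r² and the detectable difference by √(1 − r²). The t-test would need 82/(1 − r²) patients per arm to match it.

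| Assumed r | Variance left, 1 − r² | Detectable difference (SD) | t-test patients per arm to match 82 |
|---|---|---|---|
| 0.3 | 0.91 | 0.42 | 90 |
| 0.5 | 0.75 | 0.38 | 109 |
| 0.7 | 0.51 | 0.31 | 161 |
| 0.8 | 0.36 | 0.26 | 228 |

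These figures assume that every patient has a baseline test.

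**4. Patients without a baseline test.** Let f be the share with one. In a model with a common baseline mean, the information relative to the t-test is f/(1 − r²) + (1 − f). The article does not give f. For illustration, f = 0.5 gives:

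- r = 0.3: 0.5/0.91 + 0.5 = 1.05
- r = 0.5: 0.5/0.75 + 0.5 = 1.17
- r = 0.7: 0.5/0.51 + 0.5 = 1.48
- r = 0.8: 0.5/0.36 + 0.5 = 1.89

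The matching values when all patients have a baseline test are 1.10, 1.33, 1.96 and 2.78. Those are upper bounds for this trial.

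**5. Chance imbalance.** The baseline difference between arms has a standard error of 0.156 SD under randomisation. An imbalance of that size carries r × 0.156 into the unadjusted follow-up difference: 0.08 SD at r = 0.5 and 0.11 SD at r = 0.7.

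**6. The one-sample test.** Suppose it were run in each arm with 82 patients, both arms truly 0.3 SD below the norm and no difference between them. Each arm is significant with probability Φ(0.3·√82 − 1.960) = 0.775. Exactly one arm is significant with probability 2·0.775·0.225 = 0.35. A significant result in one arm only is therefore not evidence of a treatment effect.

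**The case against.** **The t-test is valid.** This stands. With 1:1 randomisation the raw-score comparison is unbiased. A reader might infer that the analysis is invalid or biased; the documents do not support that. The fault is lost precision.

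**The loss may be modest.** This also stands. A reader might infer that most of the information is thrown away. That needs r² above one half, so r above about 0.71. The article gives no r, and a tumour resection lies between the two tests, so a high value cannot be taken for granted. At r = 0.3 the loss is 9%. Patients first seen the day before surgery reduce the gain further.

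**The one-sample test is not an efficacy test.** This stands. A reader might take it for a failed attempt to compare the arms. The article says that standardised scores serve to compare patients with control participants, the step is optional, and nothing says that it will support a treatment conclusion. It only needs a label.

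**Not every other continuous outcome gets a mixed model.** Correct. Cortisol and glucose are among the laboratory secondary outcomes and have no stated model. The contrast holds for the continuous BPRS and the scales listed with it.

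**The sentence is condensed, and a statistical plan will follow.** The article names no time point for the t-test and does not exclude a baseline term in so many words. A plain t-test is still the natural reading. The article states a method here, so the point concerns a stated choice and not an omitted detail. The article also says that the statistical plan will be finalised before the analyses start, so the choice can be improved there.

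**Conclusion.** The point holds as one of efficiency and consistency on a secondary outcome. The stated comparison leaves out a baseline measurement that the trial schedules, while the article models comparable repeated scales over time.

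Among patients with a baseline test, adjustment would leave 91% to 36% of the variance for assumed correlations of 0.3 to 0.8. For the trial as a whole the gain is smaller by an amount that depends on the unknown share without baseline tests. The result rests on those assumed correlations and on reading the t-test as unadjusted. The primary chi-square test and the sample size of 180 are untouched.

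**What to change.** In the statistical plan, before unblinding:

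1. Extend the mixed linear model already planned for the other continuous scales to the neurocognitive tests. Take the baseline and 5 to 8 week scores as responses, with a common baseline mean across arms, and adjust for centre and tumour type, the stratification factors. The common mean is justified by randomisation, because the baseline tests precede the intervention. It also keeps patients without a baseline test in the analysis.
2. Use either raw or norm-corrected scores and say which. Transform skewed raw scores where needed. Norm correction after a log transformation would need norms on the log scale, which the article does not show to exist.
3. Label the one-sample comparison with norms as descriptive, and state that it does not compare the arms.

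The cost is wording in the plan and slightly more analysis. No new data are needed.

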#### Subgroup analyses

Subgroup analyses will be performed to explore differences in our primary and secondary parameters for type of tumour, gender, age and dosage of dexamethasone.

As the study remains blinded until completion, no interim analyses are planned. In addition, the statistical plan will be finalised before starting the analyses.

### Data management

All data will be collected, stored, and analysed in a coded manner, and in accordance with the General Data Protection Regulation (GDPR). Data are collected and stored in the web-based database management system Castor EDC using electronic case report forms (CRFs). The CRFs have built-in data validity and value range checks. Source documents include medical records, paper CRFs, paper interviews, questionnaires and neuropsychological tests. All data is pseudonymised with a study code and will be stored for 15 years. The subject identification log which links subjects to the code is kept in a trial file only accessible to study personnel. Possible blood samples and residual tumour tissue obtained for standard care and obtained following local consent forms during the study will be stored according to local regulatory guidelines.

### Safety

Participating in the trial is very unlikely to bring additional risks for patients, since hydrocortisone is given in a low dose to restore the physiological cortisol level in the body.

#### Data Safety Monitoring Board

This study established a DSMB that protects and guarantees patients safety during the trial. The DSMB includes three members with different study backgrounds: a statistician, psychiatrist and an internist/clinical epidemiologist. The role and responsibilities of the DSMB are described in the DSMB charter document.

#### Adverse events and serious adverse events

The study population has a high risk of complications, which are inherent to their vulnerable condition (neurological deficits caused by a brain tumour, surgery, high-dose dexamethasone), and these are considered unrelated to the intervention. The patient population is expected to encounter many AEs not related to the experimental design; therefore, not all AE will be registered. AEs that will be registered are: psychiatric reports of which psychiatric consultation and medication is needed, brain oedema for which increased dexamethasone medication is given, or for which the dexamethasone reduction scheme is extended, all infections for which antibiotics are needed, cerebrospinal fluid leakage that requires surgical intervention, hyperglycaemia for which medication is needed, cardiovascular events requiring intervention, epileptic seizures requiring intervention and secondary adrenal insufficiency that requires hydrocortisone suppletion. The abovementioned AEs will be registered from the start of the intervention until completion of the trial.

SAEs that we will record are any untoward medical occurrence or effect that result in death, are life threatening (at the time of the event), require hospitalisation or prolongation of existing inpatients’ hospitalisation — including intensive care — when a patient has unexpected longer IC admission or unexpected >10 days hospitalisation, result in persistent or significant disability or incapacity — like neurological dysfunction — lasting for more than 3 days postoperatively, result in any other important medical event not mentioned above due to medical or surgical intervention and judged as such by the investigators and postoperative haemorrhage for which recraniotomy is needed. An elective hospital admission will not be considered an SAE. Whether related to the study medication or not, all these SAEs occurring during the intervention period will be reported through the web portal governed and issued by the Dutch National Ethics Committee (The Central Committee on Research Involving Human Subjects (CCMO)) called ‘ToetsingOnline’. SAEs occurring after the intervention period will be line listed and not reported in ToetsingsOnline.

### Monitoring

According to Good Research Practice, independent on-site monitoring visits will be performed to ensure that the conduct of the trial is consistent with the approved protocol(s), the rights and well-being of the subjects are protected, source documents are verified and data are accurately reported from the source documents. Monitoring visits will take place according to the study-specific monitoring plan.

### Patients and public involvement

Patients and public were not involved in the study design. The ZonMw committee that granted the funding includes a representative of the patients interests. The committee is kept informed annually.

## Ethics and dissemination

The study protocol has been approved by the accredited Medical Research Ethics Committee of the LUMC, by the Dutch competent authority and by the Institutional Review Boards of the participating sites. Substantial amendments to the protocol will first be sent for approval, and on consent, the participating centres and trial registries will be informed. The study will be conducted according to the principles of the Declaration of Helsinki, Good Clinical Practice guidelines — including centre-specific requirements — and in accordance with the Dutch Medical Research Involving Human Subjects Act (WMO). Participant WMO subject insurance is provided by the LUMC for all participating subjects and liability insurances are provided by all participating centres. This trial is registered in the Netherlands Trial Register (NTR). Regardless of the outcome, trial results will be submitted for publication in a peer-reviewed journal and presented at conferences. Publication rights and ownership of data are secured in a clinical trial agreement with participating centres. Full protocol, data sets and statistical analyses will be available in a repository with a persistent identifier after publication of the final results.

## Trial status

The first patient was included on 10 September 2019 and recruitment is ongoing. Inclusion rate has slowed down due to the COVID-19 pandemic from March 2020 onwards. End of recruitment is expected to be 2022. The current study protocol version is V.3, 28 August 2020.

## Discussion

The DEXA-CORT trial is the first double-blind, placebo-controlled trial in adult patients with a brain tumour, in which we investigate the possible prevention of neuropsychiatric adverse effects of perioperative dexamethasone treatment. Dexamethasone is a well-known very potent activator of the GR and consequently suppresses endogenous adrenocortical cortisol production via negative feedback on the HPA-axis, depleting brain MR from its ligand.^12–14^ The resultant disturbed balance in receptor activation in the brain may predispose for psychopathology. In this study, we test the hypothesis that reinstating brain MR activity via cotreatment with a physiological dose of cortisol (=hydrocortisone) will improve (specific features of) neuropsychological well-being. Because of the high dexamethasone doses and high affinity of dexamethasone for GR, cortisol treatment will only affect MR occupancy and not interfere with the therapeutic goal of dexamethasone treatment, which is GR activation.

Adverse neuropsychiatric effects can also be present with the use of other GCs, like prednisone and prednisolone. Like dexamethasone, prednisone and prednisolone suppress the HPA-axis, which would subsequently deplete MR from its ligand. In addition, compared with the naturally produced cortisol, the synthetic GCs dexamethasone, prednisone and prednisolone all have much lower MR binding potency.^11^ An important difference between dexamethasone and the other mentioned GCs is its higher GR potency, its long half-life and lower MR potency. The potency differences could be of influence on the adverse effects; higher GR potency could suppress the HPA-axis faster, and longer half-life might extend its effects. Lower MR potency might accentuate the effect of a suppressed HPA-axis. It would be interesting to investigate the difference in neuropsychiatric effects between different GCs and (eventually) benefit of hydrocortisone add on.

This cortisol refill approach was already performed in childhood leukaemia patients. Patients who experienced severe adverse effects of dexamethasone seemed to benefit from the additional hydrocortisone medication.^21^ To establish this potential positive effect in an adult population, the DEXA-CORT trial is investigating this principle in adult patients with a brain tumour. Dexamethasone is a standard clinical treatment in patients with a brain tumour perioperatively and adverse effects are also present in this patient group, which leads to reduced HRQoL. A methodological drawback of our study population is the lack of a cross-over design. Rather, the high doses, but brief perioperative use of dexamethasone, formed the rational for testing our hypothesis in this patient group. If additional hydrocortisone to dexamethasone proves effective in reducing its neuropsychiatric adverse effects, it would offer a new treatment option for this patient group and maybe even for many other patients who receive long-term treatment with dexamethasone and other synthetic GCs. An interesting question that will follow is how long to continue the hydrocortisone replacement. After dexamethasone treatment, the endogenous HPA-axis will need a recovery period. It might be beneficial to continue the additional hydrocortisone for at least some days after dexamethasone is stopped.
